## Abstract

**Backgrounds and aims:**

Rheumatoid arthritis (RA), is immune-inflammatory disease which is associated with great pain and disability. Overproduction of pro-inflammatory cytokines and oxidative stress play an important role in RA pathogenesis and related outcomes. The aim of this study was to evaluate the effects of propolis on inflammatory biomarkers and oxidative stress status in RA patients.

**Methods/design:**

Randomized, placebo-controlled, and double-blind clinical trial aiming to recruit 48 patients with RA. Block randomization will be used. An intervention group will receive 500 mg/twice a day propolis capsules for 3 months and control group will receive the placebo for the same dose and duration. The oxidative stress status (malondialdehyde (MDA), total antioxidant capacity (TAC), total oxidant status (TOS), superoxide dismutase (SOD), catalase (CAT), glutathione peroxidase (GPx)), and inflammatory biomarkers (interleukin-17 (IL-17), Tumor necrosis factor alpha (TNF-α), High-sensitivity C-reactive protein (hs-CRP)), lipid profile (total cholesterol (TC), high density lipoprotein (HDL-c), low density lipoprotein (LDL-c), and triglyceride (TG)) and also physical activity, anthropometric indices, clinical and nutritional status will be measured at beginning and end of this study. The primary analysis will be based on theintention-to-treat principle.

**Discussion:**

If this randomized clinical trial shows the reduction in inflammatory cytokines and oxidative stress and improves clinical outcome, it would provide evidence for other clinical trials to evaluate the efficacy of propolis supplementation in RA patients.

## Introduction

1

Rheumatoid arthritis (RA) is inflammatory disease which firstly targets synovial tissues, lead to considerable pain and disability in patients. The prevalence of RA in adults is about 0.5–1.0% [1,2]. It has a considerable negative effects on the quality of life (QOL), and the ability to do daily activities [3]. The clinical studies have been shown that oxidative stress play an important role in the etiology of RA, also evidences demonstrated the increased level of oxidative stress biomarkers and decreased antioxidants status in RA patients [[4], [5], [6], [7], [8]] The reactive oxygen species (ROS) can cause inflammatory responses by activating nuclear factor kappa-B (NF-kB) in in RA [4]. Therefore, supplementation with antioxidant agents may help to relieve symptoms and improve QOL. Today's pharmacologic agents such as non-steroidal anti-inflammatory drugs, corticosteroids, and disease-modifying anti-rheumatic drugs (DMARDs) are available to alleviate RA symptoms, but these agents have some side effects [9]. Therefore, attention to adjuvant treatments, especially dietary supplements has been increased.

Propolis is a resinous hive product that is made by honeybees [10]. The composition of propolis is very complex and dependent on the plant sources [11,12]. Analysis of propolis samples from different regions has identified at least 300 different compounds. The beneficial effects of propolis are mostly attributed to the phenolic components such as flavonoids (flavonols, flavones, flavonones, dihydroflavonols), terpenes, beta-steroids, aromatic aldehydes, and alcohols [13,14]. Literature showed that propolis has positive effects on atherogenesis, diabetes, cancer, oxidative and inflammatory status [[15], [16], [17], [18], [19], [20]]. Based on the current evidences, antioxidant features of propolis is responsible for its therapeutic benefits [16,19]. It improves the antioxidant status and prevents the production of proinflammatory cytokines by inhibiting NF-kB [[21], [22], [23]].

To the best of our knowledge, there is no clinical trial that assessed the effects of propolis on biochemical and clinical status in RA, so we hypothesized that propolis would decrease serum inflammatory biomarkers, improve oxidative stress status, and clinical status. Hence, this study has been designed to investigate the efficacy of propolis administration in RA patients.

## Methods/design

2

### Trial design

2.1

This RCT protocol was written according to the CONSORT SPIRIT 2013 guidelines [24]. In the present double-blind, randomized, placebo-controlled parallel study we will include 48 women with RA. The study design is presented in Fig. 1. Subjects will be selected from patients referring to the Imam Reza hospital related to Mashhad University of Medical Sciences (MUMS) from Aguste 2020. Patients will be screening based on inclusion and exclusion criteria by an experienced rheumatologist.

**Fig. 1 fig1:**
[figure not shown]
Trial protocol

### Eligibility criteria

2.2

Eligibility criteria for RA patients will be done as follows. Participants will be allocated into two groups by block randomization.

### Inclusion criteria

2.3

-Diagnosis of the disease by a rheumatologist based on the criteria of the American College of Rheumatology [25].-Women in the age range of 20–70 years.-Identical drug advisement during study in both of groups.-Patients with moderate and severe disease activity-Participants with a history of antioxidant supplements use in three months leading to the study were also excluded-The tendency to cooperate and sign informed written consent

### Exclusion criteria

2.4

-Pregnancy and lactation-Taking oral contraceptive pills-A history of chronic diseases (i.e. cardiovascular disease (CVD), diabetes, cancer, liver or kidney disease)-Having other autoimmune and inflammatory diseases-Abnormal hormonal and thyroid disorders-Alcohol consumption and hookah smoke-Smoking and being exposed to secondhand smoke (Active or passive smokers)-Consumption of any steroidal drugs

### Baseline assessment

2.5

The study timeline is presented in Table 1. The baseline assessment related clinical status (DAS 28) will be performed by rheumatologist, then the research dietitian, who will collect demographic details, medical and social history (living situation, marital status, current occupation), Health activity questionnaire (HAQ), physical activity questionnaire, dietary intake (3 day record) assessment, anthropometric measurement (Weight, Height, body mass index (BMI), waist circumference (WC) and hip circumference (HC).

**Table 1 tbl1:**
[figure not shown]
Timeline and applied tests.

### Randomization and interventions

2.6

Eligibility of patients will be determined at the first screening visit. Block randomization method will be used for this trial study. Participants will be allocated randomly (1:1) to intervention and control groups based on random block procedure consisting of four subjects per block.

Blocking will be complemented according to patient's baseline characteristics such as severity of disease (moderate or severe), menstrual status (yes or no), BMI (BMI: <30 and ≥ 30 kg/m^2^) and type of intervention (propolis or placebo). The intervention group will receive 500 mg propolis (100 mg polyphenol compounds and 67 mg flavonoids) capsules orally twice a day and the control group will receive 500 mg placebo (corn starch) orally twice a day. The drug treatment protocol in the control group will be the same in both of groups. Also, Participants will be instructed to continue their usual diet, physical activity, and medication during the intervention.

Anthropometric indices (Body weight, BMI, WC, HC), and blood pressure will be assessed at beginning and end of intervention. The dietary intakes of patients will be assessed based on 3-day food records and convert to analytical data by Nutritionist IV program modified for Iranian foods. To evaluate the physical activity, we will be used the International Physical Activity Questionnaire (IPAQ) [26].

### Ethics approval

2.7

The study has been approved by the ethics committee of Mashhad university of Medical Sciences (ethical code: IR. MUMS.MEDICAL.REC.1399.145) and was registered in the Iranian Registry of Clinical Trials website (IRCT ID: IRCT20190407043194N2).

### Safety consideration

2.8

During the screening and follow-up any abnormalities detected will be discussed with rheumatologist involved in the study. Also, if we see any side effects after consumption of propolis, the patient will be excluded from the study. All participants will be informed of their blood test results as the study will be completed.

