### Power calculation and sample size estimates

2.9

To determine the sample size in this study, we used the previous study [27]. Also, we used from sample size formula suggested for randomized clinical trials. We considered the Type I error of 5% (α = 0.05) and Type II error of 20% (β = 0.2; power = 80%) and serum levels of MDA as a primary outcome, and we calculated the sample size of 18 persons for each group. With 30% dropout, finally twenty-four patients will consider for each group.

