### Blinding

2.10

Patients and researcher team will remain blinded to complete treatment period of 3 months. Treatment allocations will only be revealed at the end of study. The placebo capsule is similar to the study drug for taste, color, size and both of supplements manufacture with identical company (Shahdineh Golha pharmaceutical Company, Isfahan, Iran).

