### Laboratory assessment

2.13

Seven ml of venous blood will be obtained from all of patients after 10–12 h fasting at the beginning and after 3 months of intervention in the Sadra lab. The serum and plasma will be separated by centrifugation at 3000 rpm for 10 min, then the serum samples will be stored at −70 °C after centrifugation until assay. Finally, Serum hs-CRP, SOD, CAT, GPx, TNF-α, IL-17, TAC, and TOS concentrations will be quantified by the use of a commercial ELISA kit. Spectrophotometric method will be used to determine serum MDA by using the thiobarbituric acid reactive substance method [28]. Serum levels of triglycerides (TG), total cholesterol (TC), and high-density lipoprotein cholesterol (HDL-C) will be measured enzymatically. Low-density lipoprotein cholesterol (LDL-C) will be calculated by the Friedwald formula as follows [29]:

LDL cholesterol = (Total cholesterol-HDL cholesterol) – (Triglyceride/5)

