### Statistical methods

2.14

All our analyses will be based on the intention-to-treat (ITT) approach. Data will be analyzed by using the SPSS software, version 23 (SPSS Inc, Chicago, IL, USA). Quantitative data will be presented as mean ± standard deviation (SD), and qualitative data are will demonstrated as frequency and percent. The Kolmogorov-Smirnov test will be used to assess the normality of data. Paired *t*-test will be used for before and after intervention comparisons. Analysis of covariance (ANCOVA) will be applied to identify any differences between two treatment groups after adjusting for confounding variables. Results will be considered statistically significant at p-value less than 0.05.

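### Excluding patients from the study for any side effect conflicts with the intention-to-treat rule, and as worded with blinding; it can bias the comparison

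*Protocol article*

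**What the plan says.** Section 2.8 (Safety consideration) of the protocol article states: "if we see any side effects after consumption of propolis, the patient will be excluded from the study". It sets no grade or causality threshold. It does not mention the placebo arm, and it does not say whether such a patient is still measured at 3 months or still analysed.

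Section 2.14 (Statistical methods) states: "All our analyses will be based on the intention-to-treat (ITT) approach". The abstract says the same of the primary analysis.

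Section 2.10 (Blinding) states: "Patients and researcher team will remain blinded to complete treatment period of 3 months", and then: "Treatment allocations will only be revealed at the end of study". The placebo is matched in appearance and taste.

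Section 2.13 (Laboratory assessment) takes blood "at the beginning and after 3 months of intervention", and section 2.11.1 places the joint counts and visual analogue scale at the same two times. No section connects the exclusion rule with intention to treat or with blinding.

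**The concern.** Intention to treat means that patients are analysed in the arm to which they were randomised, whatever happens afterwards. Section 2.8 takes a patient out because of something that happens after randomisation and that the treatment may have caused. If the rule is followed as written, the patients compared at 3 months are those who had no side effect. Randomisation then no longer guarantees that the two groups are alike for MDA, the cytokines or DAS28.

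The loss cannot be repaired later. Outcomes are measured only at entry and at 3 months, so a patient removed in between has no end value. No analysis plan can recover a sample that was never drawn. The article's trial status section says that recruitment is under way.

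There is a second conflict. The rule names propolis alone, yet the people who apply it are not supposed to know who takes propolis.

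**Working it through.** **1. The plan's own figure.** Section 2.9 gives 18 per group, 30% dropout and 24 per group. 18 × 1.3 = 23.4, rounded up to 24, reproduces it (18 / 0.7 = 25.7, or 26, is close). The point does not rest on this figure. No MDA difference or SD is given, so 18 itself cannot be rebuilt. At 80% power and α = 0.05 (two-sided assumed, since sidedness is not stated), 18 per group implies a standardised difference of (1.960 + 0.842) × √(2/18) = 0.934 SD. It serves below only as a yardstick.

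**2. The sections side by side.**

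| Reading of section 2.8 | Against 2.14 (intention to treat) | Against 2.10 (blinding) |
|---|---|---|
| Propolis arm only, patient leaves the study | Conflicts | Conflicts: allocation must be known |
| Both arms, patient leaves the study | Conflicts | Consistent |
| Capsules stop, patient still measured and analysed | Consistent | Consistent if applied to both arms |

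Only the third reading, applied to both arms, fits all three sections, and the text does not state it.

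**3. Size of the possible bias.** Let a share q of an arm be removed, and let the mean outcome of those removed be g SD worse than that of those kept. The full-arm mean is (1 − q) × kept + q × removed, so the kept mean differs from the full-arm mean by q × g. With shares q1 (propolis) and q0 (placebo) and the same g in both arms:

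bias = (q1 − q0) × g, in favour of propolis when q1 > q0 and g > 0.

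If g differs between arms, the expression is q1 × g1 − q0 × g0, and equal rates alone do not make it zero. The documents give neither q nor g; all values below are assumptions.

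| q1 | q0 | g = 0 | g = 0.25 | g = 0.5 | g = 1.0 |
|---|---|---|---|---|---|
| 10% | 10% | 0 | 0 | 0 | 0 |
| 20% | 10% | 0 | 0.025 | 0.05 | 0.10 |
| 30% | 10% | 0 | 0.05 | 0.10 | 0.20 |
| 10% | 0% | 0 | 0.025 | 0.05 | 0.10 |
| 20% | 0% | 0 | 0.05 | 0.10 | 0.20 |
| 30% | 0% | 0 | 0.075 | 0.15 | 0.30 |

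Against the yardstick, 0.10 / 0.934 = 11% and 0.30 / 0.934 = 32%.

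**4. Effect on the type I error, one-arm reading, g = 1.0.** With 24 × (1 − q) propolis patients against 24 on placebo, the test statistic shifts by q × g / √(1/n1 + 1/24). For q = 30%: n1 = 16.8, and the shift is 0.30 / √(1/16.8 + 1/24) = 0.30 / 0.318 = 0.94. The two-sided error (normal approximation) is then about 0.156. For q = 10% and 20% it is about 0.063 and 0.100.

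**The case against.** The strongest reply is that section 2.8 is a short safety paragraph and does not define an analysis set. Exclusion there may mean no more than stopping the capsules, and a patient who stopped could still be measured and analysed as randomised. That is possible, but the text speaks of the study and not of the capsules. The point rests on two stated rules that conflict, not on detail that an article leaves to a fuller document.

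A reader might infer that the rule does remove patients from one arm only. That is the literal wording, but a team blinded under section 2.10 with a matched placebo could not apply it that way. Loose wording for study capsules in either arm is at least as likely, and the documents do not settle it.

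A reader might also infer that the comparison is certainly biased. It is not shown. Bias requires that the removed patients differ from the rest, and that the removals do not balance out between arms. The documents support neither a rate nor a direction.

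Three further inferences go too far:
- Nothing says that side effects will go unrecorded. Section 2.8 has abnormalities discussed with the rheumatologist.
- The inclusion item "Identical drug advisement during study in both of groups" is oddly placed, but no section removes a patient for a drug change.
- A shortfall in numbers is not shown. Removing 20% of 24 leaves 19.2, above the 18 required, and section 2.9 allows for 30% dropout without saying whether these exclusions count within it.

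**Conclusion.** The conflict between sections 2.8 and 2.14 stands on the wording and needs no assumption. As worded for propolis only, section 2.8 also conflicts with section 2.10. Extending the rule to both arms removes the blinding conflict but not the intention-to-treat conflict.

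The consequence is conditional: the rule can bias the comparison. With the same g in both arms, the bias is zero when removal rates are equal or when removed patients do not differ. A modest imbalance of 20% versus 10% gives 0.025 to 0.10 SD for g between 0.25 and 1.0. The upper end of the range examined, about 0.30 SD, requires 30% removal from the propolis arm alone and a 1 SD difference. The correction should still be made, because the 3-month values lost under the rule cannot be recovered.

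**What to change.** Reconcile sections 2.8, 2.10 and 2.14 in three steps:

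- Word the rule identically for both arms, in terms of study capsules, and state that it is applied without knowledge of allocation.
- Separate stopping the capsules from leaving the study. When capsules are stopped is a clinical matter and is not addressed here.
- State that every randomised patient, whether or not she still takes capsules, is invited to the planned 3-month blood draw and the DAS28 and HAQ assessments, and is analysed in the arm to which she was assigned.

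The cost is protocol wording, since the 3-month visit is already planned for everyone. The downside is that some patients who are off capsules enter the analysis, which may dilute the estimated effect slightly. In return, the selection caused by this rule is removed for every patient who attends.

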### Power calculation and sample size estimates

2.9

To determine the sample size in this study, we used the previous study [27]. Also, we used from sample size formula suggested for randomized clinical trials. We considered the Type I error of 5% (α = 0.05) and Type II error of 20% (β = 0.2; power = 80%) and serum levels of MDA as a primary outcome, and we calculated the sample size of 18 persons for each group. With 30% dropout, finally twenty-four patients will consider for each group.

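### The 24 per group said to allow for 30% dropout keeps the required 18 only up to 25% dropout; 30% would need 26 per group

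*Protocol article*

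**What the plan says.** The sample size argument is in section 2.9 of the protocol article (Power calculation and sample size estimates). It takes a type I error of 5%, power of 80% and "serum levels of MDA as a primary outcome", refers to one earlier study for its inputs, and reports the result: "we calculated the sample size of 18 persons for each group". The dropout step follows directly: "With 30% dropout, finally twenty-four patients will consider for each group".

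Section 2.1 (Trial design) carries the resulting total: "we will include 48 women with RA". The abstract also gives 48. Section 2.6 (Randomization and interventions) sets 1:1 allocation in blocks of four.

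No other section gives a different dropout rate or another reason for 24. The MDA difference, its SD, the sidedness of the test and the inflation formula are not printed.

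**The concern.** A dropout allowance should leave the required number of patients after the stated loss. Here the required number (18), the loss (30%) and the enrolled number (24) all appear in the same paragraph, and applying the loss to the enrolled number does not give back the required number.

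What is at stake is the power statement. Recruitment and dropout could both go exactly as planned and the trial would still end with fewer patients than its own calculation calls for. Someone interpreting a null MDA result would then credit the trial with slightly more power, and more tolerance of dropout, than it has.

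**Working it through.** **Inputs, all from section 2.9 unless noted**

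- Required per group: n = 18
- Dropout: 30%
- Enrolled per group: 24 (48 in total, section 2.1)
- Type I error 0.05; power 80%
- Allocation 1:1 (section 2.6)
- Assumed here: two-sided test, because sidedness is not stated

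**Step 1. Reproduce the printed 24.** Multiplying by one plus the dropout rate gives 18 × 1.3 = 23.4, rounded up to 24. This matches. That the sponsor worked this way is an inference from the match.

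**Step 2. Inflate for 30% loss among those enrolled.** n/(1 − dropout) = 18/0.7 = 25.71, rounded up to 26 per group, or 52 in total. Check: 26 × 0.7 = 18.2, which is at least 18.

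**Step 3. What 24 delivers.** At 30% dropout, 24 × 0.7 = 16.8 per group. The largest dropout that still leaves 18 is 1 − 18/24 = 25%.

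Steps 2 and 3 use only printed figures. They depend on neither the MDA effect nor its SD.

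**Step 4. Effect on power.** Without the MDA difference and SD, the standardised effect d has to be solved backwards from 18 per group at 80% power. There are two limiting cases: 18 gives exactly 80%, or the unrounded requirement was just above 17 and was rounded up to 18. For a two-sample t-test with n per group, power is the probability that a noncentral t variable with 2n − 2 degrees of freedom and noncentrality d√(n/2) exceeds the critical value.

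| Two-sided t-test | d | Power at 16 | at 16.8 | at 17 | at 18 |
|---|---|---|---|---|---|
| 18 gives exactly 80% | 0.961 | 74.9% | 77.1% | 77.6% | 80.0% |
| 18 rounded up from just above 17 | 0.991 | 77.4% | 79.5% | 80.0% | 82.3% |

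At 16.8 per group, the average number left after 30% dropout, power lies between about 77% and 79.5%.

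**Step 5. Sensitivity.** At 16.8 per group, taking 18 as exactly 80%, the normal approximation gives 77.2% two-sided and 77.6% one-sided, and the one-sided t-test gives 77.4%. With 18 rounded up from just above 17, the variants give about 79.5% to 79.6%. All are below 80%, by roughly 0.5 to 3 percentage points. With 26 enrolled (18.2 remaining) and 18 taken as exactly 80%, the two-sided t-test gives 80.5%.

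**The case against.** The best defence is that the slip hardly matters. It amounts to two patients per group, and if 18 was itself rounded up, 17 remaining patients per group give 80% to within rounding. Section 2.14 also plans ANCOVA. If the unseen calculation used unadjusted values, a covariate with correlation r to the outcome reduces the residual variance by the factor 1 − r². Making up for the fall from 18 to 16.8 needs 1 − r² = 16.8/18, so r of about 0.26. This limits the practical consequence and stands to that extent. It does not reconcile the figures: section 2.9 claims no gain from adjustment, and section 2.14 does not name baseline MDA as a covariate.

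The intention-to-treat statement in section 2.14 does not help. Blood is taken only at baseline and at 3 months (section 2.13), so a patient who drops out before the second sample adds no 3-month MDA value. Nor do blocks of four explain 24, since 52 is also a multiple of four.

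Three stronger readings are tempting, and the article does not support them:

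- **That power at 30% dropout is 77%.** This holds only if 18 gives exactly 80%, which cannot be checked without the MDA difference and SD.
- **That the allowance was calculated as 18 × 1.3.** No formula is printed. The shortfall does not depend on where 24 came from.
- **That the slip makes the trial very unlikely to keep enough patients.** If each patient drops out independently with probability 30%, the chance that both groups keep at least 18 is 0.389² = 15% with 24 per group. With 26 per group it is still only 0.627² = 39%. Much of the apparent failure is random variation that a correct allowance would leave in place, and adequate power does not require both groups to reach 18. This is not a fair measure of the error.

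**Conclusion.** The point holds as a small correction of a stated figure. The 18, the 30% and the 24 in section 2.9 cannot all stand: 24 per group covers 25% dropout, and 30% would need 26 per group, two more per group and four more in total. That conclusion needs only the printed figures and the usual reading of a dropout rate as a share of those enrolled.

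The power consequence is conditional. It assumes an unadjusted two-sample comparison, patients lost before the 3-month sample contributing no outcome, and an effect size solved back from the 18. It does not show that the trial is seriously underpowered, and the base figure of 18 itself can be neither confirmed nor disputed from the article.

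**What to change.** Keep 48 patients and replace the dropout sentence in section 2.9 with wording such as: *With 24 per group the trial keeps the required 18 per group at up to 25% dropout; at 30% dropout (16.8, or about 17, per group) power is slightly below 80% (about 77% to 79.5%, depending on rounding of the 18).* If the sponsor has the unrounded sample size from its own calculation, the range can be replaced by a single figure.

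The cost is one sentence. Enrolment had already begun (Trial status section), and no extra patients or change to the conduct of the trial is needed. The stated property becomes slightly less favourable, and 80% power at 30% dropout is no longer claimed.
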